# Engaging Fathers for Effective Child Nutrition and Development in Tanzania (EFFECTS): study protocol for a five-arm, cluster-randomized trial

**DOI:** 10.1186/s13063-022-07002-4

**Published:** 2024-03-14

**Keywords:** Early child development, Dietary diversity, Nutritional status, Father engagement, Tanzania

## Abstract

**Background:**

Globally, 144 million children under 5 years are undernourished and 250 million do not meet their developmental potential. Multi-input interventions, such as bundled nutrition and parenting interventions, are designed to mitigate risks for multiple child outcomes. There is limited evidence that bundled interventions have additive benefits to nutrition, growth, or development outcomes. These outcomes share common risks; therefore, designing interventions to tackle these risks using a common theory of change may optimize effectiveness. Emerging evidence suggests explicit engagement of fathers may benefit child outcomes, but few trials have tested this or included data collected from fathers.

**Methods:**

Engaging Fathers for Effective Child Nutrition and Development in Tanzania (EFFECTS) is a community-based cluster-randomized controlled trial that will be implemented in the rural Mara Region, Tanzania. The trial aims (1) to test a bundled nutrition and parenting program delivered to mothers’ groups, with or without fathers’ groups, over 12 months on child and caregiving outcomes compared to a nutrition program alone, and (2) to test nutrition or bundled nutrition and parenting programs delivered to mothers’ and fathers’ groups over 12 months on child and caregiving outcomes compared to programs delivered to mothers alone. The trial comprises five arms: (1) mothers’ groups receiving a nutrition program, (2) mothers’ groups receiving a bundled nutrition and parenting program, (3) mothers’ and fathers’ groups receiving a nutrition program, (4) mothers’ and fathers’ groups receiving a bundled nutrition and parenting program, and (5) control receiving standard of care health services. The primary outcomes are child dietary diversity and early child development (mental and motor development). Parents with a child under 18 months will be enrolled in peer groups and receive twice monthly intervention by trained community health workers. Data will be collected from mothers, fathers, and children at baseline (pre-intervention), midline, and endline (post-intervention).

**Discussion:**

EFFECTS will generate evidence on the effects of bundled nutrition and parenting interventions on child nutrition, growth, and development outcomes; determine the benefits of engaging fathers on child, caregiving, and caregiver outcomes; and investigate common and unique pathways between treatments and child outcomes.

**Trial registration:**

ClinicalTrials.gov NCT03759821. Registered on November 30, 2018

**Supplementary Information:**

The online version contains supplementary material available at 10.1186/s13063-022-07002-4.

## Background

Globally, 144 million children are chronically undernourished and 250 million children do not meet their developmental potential in the first 5 years of life [1, 2]. Poor early nutrition and development can have lasting consequences on developmental trajectories, educational attainment, adult physical and mental health, and earning potential [3, 4]. While malnutrition is a significant risk factor for poor child development, nutrition interventions alone tend to show small effects on early child development (ECD) outcomes [5–7]. On the other hand, parenting interventions (with a focus on stimulation and responsive caregiving) tend to have modest-to-large effects on children’s mental development. Promoting optimal nutrition behaviors with positive parenting behaviors and couples’ communication could improve children’s development, nutritional status, and growth. From a policy and program perspective, bundled nutrition and early childhood programs have the potential to be resource efficient [8]; however, further evidence is needed to optimize bundling of intervention components.

A prior review on integrated nutrition and early childhood development interventions concluded that (a) nutrition interventions benefitted child growth and nutritional status and had some smaller benefits on ECD, (b) stimulation interventions benefitted ECD, (c) there was limited evidence for additive effects of integrated nutrition and stimulation interventions on either child growth or early child development, (d) there was no evidence for harm as a result of integrated nutrition and stimulation interventions, and (e) evidence was limited on the long-term impact of early interventions implemented either as single focus interventions or as integrated packages. Therefore, the case for integrated interventions is not based on the effect on a single outcome, but on the need to impact multiple child outcomes. Tackling common risks for poor child nutrition and ECD, which include maternal depression and inadequate responsive care in addition to lack of access to resources and an enabling environment, is one approach to designing improved integrated nutrition and parenting programs [9, 10]. An explicit shared theory of change and behavior change techniques are likely necessary in the design of complex multi-input interventions in addition to considerations for the number of messages that can be effectively and feasibly delivered [11–13].

Traditional public health programming has typically emphasized nutrition education for women, particularly in their reproductive years, without addressing the socio-cultural, gender, and decision-making norms and practices that prevent families from adopting and maintaining new behaviors, hence failing to ensure an enabling environment for behavior change. Fostering an enabling environment requires a shift from mother-focused programs to family-based programs and in particular the engagement of fathers [14, 15]. Fathers support their children’s nutrition and development through multiple ways, including financial support, childcare, and protection. The degree of shared responsibilities, decision-making regarding household income-generating activities and resource use, nutrition knowledge and support, and emotional care provided by fathers can enhance maternal caregiving capabilities, family relationships, household food access, and the home environment, which can in turn promote child outcomes [16–26]. Few studies have included fathers in parenting programs that incorporate care for child nutrition; however, while these studies demonstrate benefits to child outcomes, there is no report on potential ways the engagement of fathers may have contributed to the program effects [27, 28]. A recent randomized controlled trial from Rwanda that engaged fathers through couples’ communication and decision-making, male engagement in maternal and child health, and violence prevention found improvements in women’s attendance and men’s accompaniment at antenatal care visits, fathers’ engagement in household responsibilities, and couples’ relationships and reduced fathers’ violence against women and children [29]. Taken together, these studies suggest engaging and supporting fathers can have transformative benefit to child outcomes, caregiver well-being, and family functioning. However, a limitation of these studies is the lack of data collected directly from fathers.

By engaging the household decision-makers—women and men—to understand how they can improve the nutrition, health, and development of their child, the Engaging Fathers for Effective Child Nutrition and Development in Tanzania (EFFECTS) trial will test a package of nutrition and nurturing care interventions that adopt a bundled approach to child and family well-being, moving beyond the traditional nutrition and parenting program paradigms. EFFECTS will implement intervention packages that engage fathers as well as mothers and address the multiple proximal and distal factors in the enabling environment that may hinder optimal child nutrition, nurturing care, and access to resources. These intervention packages will be delivered by community health workers in rural communities in the Mara Region of Tanzania, and effects on outcomes for infants and young children, as well as their mothers, fathers, and households, will be determined using a cluster-randomized controlled trial.

### Objectives and hypotheses

The EFFECTS study has four objectives:To test a bundled nutrition and parenting program delivered to mothers’ groups, with or without fathers’ groups, over 12 months on young child and caregiving outcomes compared to a nutrition program aloneTo test nutrition or bundled nutrition and parenting programs delivered to mothers’ and fathers’ groups over 12 months on young child and caregiving outcomes compared to programs delivered to mothers aloneTo determine the factors related to caregiving knowledge, practices, and skills; caregiver well-being; and access to and control over resources that mediate or moderate program effectsTo evaluate the fidelity of implementation with respect to training and supervision, content delivered, dose delivered, and adoption of promoted behaviors

We hypothesize that the bundled nutrition and parenting program will have greater benefits to child nutrition and ECD outcomes than the nutrition program alone. Furthermore, we hypothesize that programming delivered to both mothers and fathers will have greater benefits to child nutrition and ECD outcomes than programming delivered to mothers alone.

## Methods

The EFFECTS study is a collaboration among the African Academy for Public Health (AAPH), Global Communities (formerly Project Concern International, PCI), Harvard T.H. Chan School of Public Health, Purdue University, and the Tanzania National Institute for Medical Research (NIMR) comprising a multi-disciplinary team. Methods are described according to the SPIRIT Guidelines.

### Trial design

This cluster-randomized controlled trial will use a 2×2 factorial design, plus a local standard of care control group, to evaluate the effectiveness of EFFECTS interventions. There will be a total of five study arms. Eighty villages will be randomly assigned in equal numbers to one of the five arms:Nutrition behavior change intervention delivered through peer groups of mothersNutrition behavior change intervention delivered through peer groups of both mothers and fathersNutrition and parenting behavior change intervention delivered through peer groups of mothersNutrition and parenting behavior change intervention delivered through peer groups of both mothers and fathersControl arm receiving local standard of care

The EFFECTS study design will enable the individual and combined comparison of two strategies: (1) a bundled nutrition and parenting curriculum compared to a nutrition only curriculum and compared to the local standard of care and (2) the active engagement of fathers in both a bundled nutrition and parenting curriculum and a nutrition only curriculum compared to delivering these curricula to only mothers and compared to the local standard of care. All participating households in the five study arms will be assessed at baseline (prior to the start of any interventions), after 6 months of intervention (“midline” or “6 months”), and after the completion of 12 months of intervention (“endline” or “12 months”). Cluster randomization, rather than individual randomization, will be used as interventions will be delivered to peer groups of parents, rather than individual parents. Randomization at the village level also reduces the likelihood of spillover effects, in which knowledge gained through behavior change interventions is shared with individuals assigned to a different study arm, as families are less likely to interact with others in a different village than in the same village. Given the nature of these community-based interventions, blinding will not be possible except for outcome assessors, who will not be made aware of villages’ assignments to study arms.

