**Fig. 2 Fig2:**
[figure not shown]
The EFFECTS process evaluation framework

The EFFECTS process evaluation started with documentation of the training and will continue throughout implementation in the four EFFECTS intervention arms. An overview of the process evaluation data collection tools is presented in Table 3. Depending on the type of process evaluation data, data will be collected by either the CHWs, PCI field supervisors (FS), or two PCI monitoring and evaluation (M&E) officers at specific times during the implementation of the peer group sessions. While the FS are the direct supervisors and mentors of the CHWs, the PCI M&E officers function more independently as they are not directly linked to any specific group of CHWs nor do they provide routine technical (content/behavior change) support to the CHWs. The team of CHWs, FS, and M&E officers is independent of the outcome evaluation team. Data are collected routinely by the CHWs, FS, and M&E officers on tablets with limited paper-based data collection (e.g., pre- and post-training knowledge).

**Table 3 Tab3:** EFFECTS process evaluation data collection tools. *CHWs* community health workers, M*&*E monitoring and evaluation, *PM* project manager

Acronym and form #	Form name	Collected by	Respondent type	Frequency	Framework addressed	Key variables of interest

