**Context**						
VPS	Village programs and services	Outcome evaluators	Village leaders, market chairperson	Baseline and endline	Context	Programs and services previously and currently available at the village level by treatment arm; distance to services; activity level of services; satisfaction with services
MSQ	Market survey questionnaire	Outcome evaluators	Market vendors	Baseline and every 6 months	Context	Availability and price of key foods at the village level; market diversity; travel time to market from an individual household
FES	Food expenditures form		EFFECTS participants		Context	
PGF	Participation in group activities	Outcome evaluators	EFFECTS participants	Baseline and every 6 months	Context	Presence of groups (livelihood, savings, women’s, youth, religious, etc.) in community; active membership by the participant; participation in food or other aid programs; receipt of nutrition, health, or agriculture information, and source of information
CCY (1)	Community calendar yearly	Field supervisors	Village and community leaders	Monthly	Context	By month and season, food aid, agricultural, health, nutrition information, key local events, religious/cultural festivals, contacts with other CHWs (captures type and frequency by month)

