**Fidelity—dose received**						
PGA (6)	Peer group attendance register	CHWs	Peer group participants	Beginning of each bi-weekly peer group session	Dose received (structure and quantity)	Participant attendance (male and female); can be used to assess equality of reach but depends on demographic data we collect (Purdue/Harvard will have to do this)
HVLSR (7)	Home visit log and session report	CHWs	Peer group participants	After every home visit is conducted	Dose delivered, dose received (structure/exposure)	For participants who miss group sessions, documents home conducted by CHW, content/messages received during home visits, reasons for missing session, challenges faced by the participant
TERM (8)	Study termination form for participants	CHWs	Peer group participants	If/when a participant drops out of the study	Dose received (quantity and exposure)	ID # of dropped; CHW, date dropped; reason for withdrawal and duration in the study
PGE (9)	Participant group evaluation form	M&E officers	Peer group participants	5% of participants every month	Dose received (exposure and satisfaction); also covers aspects of spillover and community demand	Participant feedback on facilitation and satisfaction (delivery, encouraged to participate openly, topics relevant/important, perception of CHW knowledge, enough time during session, practices that are easy/difficult, likelihood of practicing the behaviors); includes 2 items from SNF that ask: “Have you shared what you discussed in the EFFECTS parents’ sessions with anyone else?” and if yes, “What is this person or persons’ relationship to you?” (SNF will also be administered as part of outcome evaluation with addition question of: “would you recommend this intervention to family/friends?”
PGSF (refer to outcome forms)	Peer group social support form	Outcome evaluators	Intervention participants	Every 6 months (outcome evaluation)	Dose received (exposure and satisfaction)	A 9-item scale measuring social cohesiveness of peer groups

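### Outcome evaluators declared blind to village allocation are assigned a form that only intervention participants receive, so blinding of the intervention-versus-control contrast is not secured

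*Protocol article*

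**What the plan says.** Trial design allows one exception to an otherwise open trial: "blinding will not be possible except for outcome assessors, who will not be made aware of villages’ assignments to study arms".

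Table 3, under dose received, lists the "Peer group social support form". Its collector is "Outcome evaluators", its respondents are "Intervention participants", and its timing is every 6 months as part of the outcome evaluation. The content is given as "A 9-item scale measuring social cohesiveness of peer groups".

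The row for the participant group evaluation form adds that the "SNF will also be administered as part of outcome evaluation", with a further question on whether the respondent would recommend the intervention. The community demand row of the same table also puts the SNF in the outcome evaluation.

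On staffing, Process evaluation says: "The team of CHWs, FS, and M&E officers is independent of the outcome evaluation team". Outcome evaluation describes a trained data collection team that interviews parents at home, and says that two enumerators assess child development at a central point in the community.

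**The concern.** Participants and community health workers know their arm, so assessor blinding is the only masking the trial has. Both primary outcomes pass through an assessor: the number of food groups comes from a recall of the previous day, and the BSID-III is scored by an examiner. If the team declared blind must know which households are peer group members in order to give them a form, the declaration conflicts with the data collection scheme in the same article. The report would then claim masked assessment that its own table contradicts, and any assessor expectation would enter the comparison with control unchecked. Outcome evaluation also says that outcome data get no quality assurance from outside the study team.

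**Working it through.** No sample size or power figure is at issue. The check sets the statements side by side and follows what the form discloses.

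**1. Is the form restricted to intervention arms?** Yes. Its respondents are labelled intervention participants, whereas the group participation form, which the same evaluators collect, is labelled for EFFECTS participants generally. The peer groups it asks about exist only in the four intervention arms; Control/standard of care describes routine services only.

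**2. When does it disclose?** It presupposes a functioning peer group, so it applies at midline and endline, not baseline. A shift that arises only after baseline is not removed by a difference-in-differences analysis.

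**3. How many villages?** Sample size/power calculation gives 16 villages per arm.
- Mothers' groups: 4 × 16 = 64 villages. Control: 16. Total 80.
- Fathers' groups: 2 × 16 = 32 villages.
- Groups in all: 64 + 32 = 96, which agrees with Intervention delivery.

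Giving or not giving the form separates 64 villages from 16. If fathers receive it too, it also separates the 32 couples villages from the 32 mothers-only villages. It carries nothing on nutrition-only versus bundled content.

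**4. Which contrasts are reached?** Let δ be an assessor shift applied to any village known to be an intervention village, and γ an extra shift where fathers are known to be engaged (γ = 0 if fathers do not receive the form). Neither has a value in the document.

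| Research question (Analysis plan) | Shift in the contrast | Result |
|---|---|---|
| 1. Any intervention vs control | [2δ + 2(δ + γ)]/4 − 0 | δ + γ/2 |
| 2. Both parents vs mothers only | (δ + γ) − δ | γ |
| 3. Bundled vs nutrition only | [δ + (δ + γ)]/2 − [δ + (δ + γ)]/2 | 0 |
| 4. Interaction | γ − γ | 0 |

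The certain exposure is question 1. Question 2 is exposed only if fathers receive the form. Questions 3 and 4 are untouched as long as the shift does not depend on content, which these forms do not reveal.

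**5. Which outcomes?** The dietary recall is presumably part of the home questionnaires, given by the staff who would also give the form, so it is the clearest case. Child development is assessed elsewhere by a pair of enumerators, and the article does not say whether they are the same people.

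**6. Does any text resolve it?** The statement of independence separates implementation staff from the outcome team. It describes no split within the outcome team, and nothing places the form after the outcome measurements.

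**The case against.** The strongest reply is that form order and staff rosters are operational detail that an article may leave to the full protocol, and that silence on them is not a documented failure. That stands in part. It rules out the stronger reading that blinding of both primary outcomes fails by design: a separate BSID-III pair, or a form given last, would preserve some of it. It does not remove the conflict, because the article itself states who collects the form, from whom and when.

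Other readings go further than the text:
- **Village services form.** A reader might infer from "Programs and services previously and currently available at the village level by treatment arm" that outcome evaluators record the arm. The phrase sits in the column of key variables and may only describe how the data will be tabulated; no form field holding the arm is shown.
- **SNF.** For its use in the outcome evaluation, the table names neither collector nor respondents. That outcome evaluators give it to intervention households is inferred from its wording, so it supports the point but does not carry it.
- **All comparisons compromised.** Both hypotheses in Objectives and hypotheses compare intervention arms with each other. Knowing only that a village is not a control gives no reason to favour one intervention arm.
- **A bias in SD units.** On the stated 0.43 food groups for a pairwise comparison, the detectable difference for four arms against control scales to 0.43 × √[(1/4 + 1)/(1 + 1)] = 0.43 × √0.625 = 0.34. The document offers no assessor shift to set against it, so any percentage would rest on an invented numerator.

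**Conclusion.** The blinding statement in Trial design and the peer group form row of Table 3 contradict each other. Masking is not secured for the intervention-versus-control contrast at midline and endline, across 64 intervention and 16 control villages, and the dietary recall is the most exposed outcome. Exposure of couples versus mothers-only arms depends on fathers receiving the form; bundled versus nutrition-only is not disclosed by these forms. BSID-III assessors may or may not be affected. The size of any bias is unknown.

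This rests on three assumptions: the table's collector and respondent entries mean what they say, the people called outcome evaluators there include the outcome assessors of Trial design, and the dietary recall is taken by the home interviewers.

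**What to change.** Reconcile Trial design with Table 3:
- Release the peer group form and the SNF on the tablet only after the last dietary recall and BSID-III in that village are locked for the round.
- Do not send an evaluator who gave these forms at midline back to the same village at endline; otherwise the midline knowledge carries over. The same should hold for control villages, since the absence of the forms is equally informative.
- State whether the BSID-III enumerators are separate from the home interviewers.
- For rounds already completed, restrict the blinding statement to the assessors and contrasts for which it held. Trial status dates the current version September 2020, and under COVID-19 only six of the 24 sessions remained in March 2020, so midline had probably passed and this may be the main remaining step.

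The cost is some scheduling inconvenience and a sentence of text. Handing the forms to the monitoring and evaluation officers is not a cheap substitute. There are two of them, and they evaluate 5% of participants a month; 96 groups × 12 members = 1,152 respondents per round is 1/0.05 = 20 times that monthly load.

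Re-sequencing will not prevent all unmasking. Evaluators also ask participants in general about group membership and sources of nutrition information, and the answers may reveal the arm.
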